##### CR vs. treatment as usual

The mean differences in outcomes of both groups combined will be compared to the waitlist period using multilevel modeling to assess the effect of CR over treatment as usual. A two-level model will be built with subject (level 2) and time point of assessment (level 1) entered as levels. The significance of the fixed regression effects is tested using the appropriate *t-*test (*α* = .05).

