**Methods:**

This is a pragmatic, triple-blinded, randomized, sham-controlled, pilot trial following a non-concurrent multiple baseline design with the participants serving as their own control. We will compare (1) CR to treatment as usual, (2) active/sham tDCS+CR to treatment as usual, and (3) active tDCS+CR to sham tDCS+CR. Clinical relevance, feasibility, and acceptability of the use of CR and tDCS will be evaluated. We will recruit 26 service users aged 18 years or older, with a SMI and dependent on residential facilities. After a 16-week waiting period (treatment as usual), which will serve as a within-subject control condition, participants will be randomized to 16 weeks of twice weekly CR combined with active (*N* = 13) or sham tDCS (N = 13). Cognitive, functional, and clinical outcome assessments will be performed at baseline, after the control (waiting) period, directly after treatment, and 6-months post-treatment.

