**Discussion:**

The addition of cognitive interventions to treatment as usual may lead to long-lasting improvements in the cognitive and daily functioning of service users dependent on residential facilities. This pilot trial will evaluate whether CR on its own or in combination with tDCS can be a clinically relevant addition to further enhance recovery. In case the results indicate that cognitive performance can be improved with CR, and whether or not tDCS will lead to additional improvement, this pilot trial will be extended to a large randomized multicenter study.

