### Objectives {7}

#### Primary objective

The primary objective of this pilot trial is to assess the potential clinical relevance of a full-scale trial to investigate the effectiveness of CR training with CIRCuiTS on cognitive and daily functioning in a population of service users with severe mental illness that requires long-term intensive psychiatric treatment and support in a clinical setting. The feasibility and acceptability of CIRCuiTS will be evaluated using pre-specified criteria. Additionally, we aim to obtain preliminary data on the effects of CR on cognitive and daily functioning.

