### Trial design {8}

The trial is designed as a pragmatic, randomized, controlled, pilot trial following a non-concurrent multiple baseline design with the participants serving as their own control. Participants will be randomized over two conditions: CR + sham tDCS (group 1) or CR + active tDCS (group 2) with a 1:1 allocation ratio, see Fig. 1. The trial will start with a waiting period of 16 weeks for all participants, which serves as a within-subject control condition, and is followed by the allocation of the participants to one of the treatment groups. During the next 16 weeks, the participants will receive 32 sessions of the allocated intervention. The participants will be invited back for a follow-up measurement 6 months post-treatment. In case of positive indications, we will extend the trial into a multicenter trial using the same design and recruit more participants.

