#### Treatment procedure

The duration of each training session will be 20–45 min increasing over time depending on the participants’ attention span and will be given twice weekly for 16 weeks. Participants will receive active/sham tDCS during the first 20 min of the CIRCuiTS training sessions. Evidence suggests that prolongation of treatment stimulation might not result in greater stimulation effects but can even result in smaller stimulation effects [41]. For convenience, the tDCS device will be kept in place for the whole duration of each session. The tDCS stimulation and the CIRCuiTS training will both be administered by the CIRCuiTS therapist. In every session, the participants’ mood, amount of sleep, severity of auditory hallucinations, and motivation will be assessed. Additionally, at the end of every session, the participants will be asked about sensations or side-effects of the tDCS.

The treatment procedures may be adapted at the time of the treatment to match the COVID-19 regulations and recommendations of the Dutch National Institute for Public Health and the Environment and of the Dutch Central Committee on Research Involving Human Subjects. Additionally, the guidelines for tDCS research through the COVID-19 pandemic [42] will be consulted. Necessary adaptations to the protocol will be described in the results paper and the trial register.

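### The contrast labelled as the effect of CR over usual care pools both arms, so it estimates CR plus half of any active-tDCS effect; no inferential contrast is named for CR without active tDCS

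*Protocol article*

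**What the plan says.** The abstract (Methods) announces three comparisons: "We will compare (1) CR to treatment as usual, (2) active/sham tDCS+CR to treatment as usual, and (3) active tDCS+CR to sham tDCS+CR". The abstract's Discussion adds: "This pilot trial will evaluate whether CR on its own or in combination with tDCS can be a clinically relevant addition".

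The Trial design section randomises participants after the waiting period to "CR + sham tDCS (group 1) or CR + active tDCS (group 2) with a 1:1 allocation ratio". Under Treatment procedure, "Participants will receive active/sham tDCS during the first 20 min of the CIRCuiTS training sessions", so every participant has either active or sham stimulation during CR.

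The statistical methods {20a} contain two outcome models:

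- Under *CR vs. treatment as usual*, the text reads: "The mean differences in outcomes of both groups combined will be compared to the waitlist period". It says that this is to be done "using multilevel modeling to assess the effect of CR over treatment as usual".
- Under *CR + active tDCS vs. CR + sham tDCS*: a multilevel comparison of group 1 with group 2.

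The section on cognitive and functional outcome measures also provides means and standard deviations for each training condition. The section on additional analyses {20b} plans none.

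The effect of CR stands under the primary objective, after feasibility and acceptability: "Additionally, we aim to obtain preliminary data on the effects of CR on cognitive and daily functioning".

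**The concern.** The label and the analysis set do not match. Half of the pooled sample is allocated to a second treatment that the Background expects to enhance learning and prolong the gains. A contrast that averages over both arms is comparison (2) of the abstract, but the statistics section gives it the label of comparison (1). The second model is comparison (3). No named contrast with the waiting period remains for comparison (1), or for the question about CR on its own.

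At stake is how the preliminary signal is read. The abstract ties extension to an indication that CR improves cognitive performance, and the Trial design section would extend the trial with the same design. If active tDCS helps, the pooled figure flatters CR; if it hinders, CR looks worse than it is. The 6-month results are exposed in the same way, because the protocol expects tDCS to make gains last longer.

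**Working it through.** **Inputs from the protocol**
- Allocation 1:1, 26 participants, 13 per arm (Trial design; Sample size).
- CR effect 0.45 SD for cognition and 0.42 SD for daily functioning, from the cited meta-analysis (Sample size).
- Randomisation after T1 (Concealment mechanism; Implementation).

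**Assumptions, not in the documents**
- Active-tDCS add-on d between 0 and 0.4 SD.
- Equal correlation r between visits, 0.7 in the main case, with unit variance at each visit.
- Contrast with the waiting period taken as (T2 − T1) − (T1 − T0).

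**Reproducing the plan's figure.** 10 / (1 − 0.20) = 12.5, rounded up to 13 per arm, and 2 × 13 = 26. This agrees. The 10 per arm is a rule of thumb from a cited source, so there is no power figure to reproduce.

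**What the pooled contrast estimates.** Let c be the change due to CR with sham, so that the active arm changes by c + d. With equal numbers:

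pooled = 0.5 × c + 0.5 × (c + d) = c + d/2

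| assumed d | bias d/2 | pooled, c = 0.45 | pooled, c = 0.42 |
|---|---|---|---|
| 0 | 0 | 0.45 | 0.42 |
| 0.2 | 0.10 | 0.55 | 0.52 |
| 0.4 | 0.20 | 0.65 | 0.62 |

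The same d/2 enters a plain T2 − T1 change, so the result does not depend on the form of the contrast. If CR did nothing and d were 0.3, the pooled value would be 0.15 SD, all of it from tDCS. With 20 completers, the chance of a two-sided 5% rejection would then be 6.6% at r = 0.5, 7.6% at r = 0.7 and 13% at r = 0.9.

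**Precision of the alternatives (r = 0.7, 13 per arm)**

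- Variance of the contrast per person: 6 × (1 − 0.7) = 1.8.
- Pooled: SE = √(1.8/26) = 0.263.
- Sham arm alone: SE = √(1.8/13) = 0.372. Ratio √2 = 1.41.
- Joint model with common means at T0 and T1: the CR + sham contrast is the pooled contrast minus half the baseline-adjusted arm difference, and the two parts are independent.
  - Residual variance of T2 given T0 and T1: 1 − 2 × 0.7² / (1 + 0.7) = 0.4235.
  - Variance of the arm difference: 0.4235 × 2/13 = 0.0652.
  - Variance of the CR + sham contrast: 0.0692 + 0.0652/4 = 0.0855, so SE = 0.292. Ratio 0.292/0.263 = 1.11.

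**The case against.** Several points on the other side are sound.

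- The pooled contrast is a legitimate average effect, it uses all participants, and the text says openly that the groups are combined. That supports keeping it, but not the label of CR over treatment as usual.
- CR efficacy is preliminary here. It sits beside feasibility and acceptability, and the numerical thresholds under Feasibility concern retention and participation only. A reader might take the pooled contrast for the trial's one primary test, and the objectives do not support that.
- A reader might infer that the CR effect can never be estimated. The documents do not support that either. Means per condition are planned, the two-group model would in a usual form contain the sham arm's change, and the design identifies the contrast. What is absent is a named inferential contrast with the waiting period.
- A reader might infer that the main trial would be sized on an inflated CR estimate. No section says so: the effect size cited comes from a meta-analysis, and the Sample size section says only that pilot data may be included in an extended trial.
- The size rests on an assumed tDCS effect. A bias of 0.10 to 0.20 SD is smaller than one pooled standard error (0.263).

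One possible defence does not stand. A null active-versus-sham result could not justify pooling afterwards, because the Discussion concedes low power for that comparison. Nor does the plan make pooling depend on it.

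**Conclusion.** The point holds as a mismatch between an analysis and its stated meaning. The pooled contrast estimates CR plus half of any active-tDCS effect and equals the CR effect only if that effect is zero. This follows from the 1:1 allocation, with equal retention in the arms, and needs no power assumption.

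The size is conditional: 0 to 0.20 SD for an assumed add-on of 0 to 0.4 SD. Against a CR effect of 0.45 SD, an add-on of 0.2 to 0.4 SD would mean an overstatement of 22% to 44% (0.10/0.45 and 0.20/0.45). These percentages illustrate the mechanism; they are not findings about this trial.

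A reader might also take the sham arm to show CR on its own. It shows CR with sham stimulation, because no arm receives CR without the tDCS procedure. It is the closest estimate the trial can give. The consequence is a possibly misread preliminary signal, and it can be repaired in the analysis.

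**What to change.** Replace the separate models with one multilevel model. It has time and arm-by-time terms after T1 and common arm means at T0 and T1, which is justified because randomisation follows T1. Against the waiting period, report:

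1. CR + sham tDCS, labelled as such and described as the closest available estimate of CR alone;
2. CR + active tDCS;
3. the difference between (2) and (1).

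Keep the pooled contrast as secondary, relabelled *CR with active or sham tDCS versus treatment as usual*. Align the abstract's three comparisons with these names.

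The change is to analysis wording only, with no added visit, participant or procedure. Allocation stays sealed until data collection is complete, so it can be made before unblinding. The price is precision: the CR + sham interval is about 11% wider than the pooled one in the joint model (assumed r = 0.7), or 41% wider if only sham-arm data are used.

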##### CR + active tDCS vs. CR + sham tDCS

The mean differences in outcomes between groups 1 and 2 will be compared using multilevel modeling to assess whether active tDCS in combination with CR is superior in improving cognitive functioning and daily functioning over CR + sham tDCS. A two-level model will be built with subject (level 1) and time point of assessment (level 2).

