#### Secondary outcomes

##### Superior effect of active tDCS

The difference between CR + active tDCS and CR + sham tDCS in the change of daily and cognitive functioning will be assessed by the same measures described above.

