### Sample size {14}

For this pilot trial, the sample size is based on Whitehead et al. [56], who evaluated and compared methods for sample size calculation for pilot studies in order to minimize the recruitment of participants across pilot and main trial while maintaining the average power. The authors advise a pilot sample size of 10 participants per treatment arm if the estimated standardized effect size of the main trial is medium or large. We estimated a medium effect size based on the results of a large meta-analysis that demonstrated moderate effects of CR on cognition (effect size 0.45) and daily functioning (effect size 0.42) [18]. Taking into account a drop-out percentage of 20%, a total of 26 participants are required in order to reach a sample size of 10 participants who complete the trial per treatment arm. By considering the pilot study as a part of the main trial, this method allows to include the pilot data, if the trial is extended to a large randomized trial with a similar design.

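### The model for active versus sham tDCS nests subjects within time points, so as written it ignores within-person correlation and gives wrong standard errors for the only randomised comparison

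*Protocol article*

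**What the plan says.** Under Statistical methods {20a}, the protocol article describes two multilevel models in consecutive paragraphs.

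- **CR vs. treatment as usual:** "A two-level model will be built with subject (level 2) and time point of assessment (level 1) entered as levels".
- **CR + active tDCS vs. CR + sham tDCS:** "A two-level model will be built with subject (level 1) and time point of assessment (level 2").

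Both models use the same people and the same visits. The abstract gives the schedule: "Cognitive, functional, and clinical outcome assessments will be performed at baseline, after the control (waiting) period, directly after treatment, and 6-months post-treatment". That is four assessments per participant, T0 to T3.

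Under Superior effect of active tDCS, among the secondary outcomes, the target of this comparison is given as follows: "The difference between CR + active tDCS and CR + sham tDCS in the change of daily and cognitive functioning will be assessed". Randomisation applies to this comparison only. Trial design {8} states: "Participants will be randomized over two conditions: CR + sham tDCS (group 1) or CR + active tDCS (group 2) with a 1:1 allocation ratio". The comparison of CR with usual treatment instead uses each participant's own waiting period.

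**The concern.** In a two-level model the upper level is the cluster, and units at the lower level are independent given their cluster. The CR paragraph follows this: visits are the lower units and the person is the cluster. The tDCS paragraph reverses it. The four time points become the clusters, the 26 people become independent units within each time point, and no term ties together the four scores of one person. The CR paragraph uses level 2 for the upper unit, so the difference cannot be explained as another numbering convention.

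The standard error, confidence interval and p-value of the active-versus-sham contrast are at stake. The Discussion links a later multicentre trial to whether tDCS seems to add to CR, and Sample size {14} allows the pilot data to be carried into a main trial. A wrong error structure here could therefore affect both the go-ahead reading and the later analysis.

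**Working it through.** **The plan's own figure.** Sample size {14} takes 10 completers per arm and 20% drop-out: 10 / 0.8 = 12.5, rounded up to 13 per arm, 26 in total. This reproduces and does not depend on the level order.

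**Inputs from the document.** Four time points; 13 per arm randomised, 10 per arm completing; effect size 0.45. That effect is the cited meta-analysis figure for CR on cognition, "moderate effects of CR on cognition (effect size 0.45) and daily functioning (effect size 0.42"), and not an estimate for tDCS. It serves here only as a yardstick. The 0.05 test level is given only in the CR paragraph.

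**Assumptions.** Total SD 1; equal correlation ρ between any two scores of one person, 0.7 with a range of 0.5 to 0.9 (the document gives none); two-sided 5% tests; complete data.

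**What the reversed model does.** A random effect for time point shifts both arms equally at a visit, so it cancels from any arm difference. If time is also a fixed effect, the random one is redundant and the fit reduces to ordinary least squares on independent rows. In both cases each row enters with variance 1 and zero correlation with the same person's other rows.

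**(a) Group difference in change between two visits (the stated target), n per arm**

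- Correct levels: SE = √(4(1−ρ)/n).
- As written: SE = √(4/n).
- Ratio: 1/√(1−ρ) = 1.41, 1.83 and 3.16 at ρ = 0.5, 0.7 and 0.9, for any n.
- False rejection as written: 2·P(Z > 1.96/√(1−ρ)). At ρ = 0.5 this is 2·P(Z > 2.77) = 0.6%. At ρ = 0.7 it is 2·P(Z > 3.58) = 0.03%. Simulation gives about 0.7% and 0.1%; it is higher because the residual variance is estimated.

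Power for 0.45 SD at ρ = 0.7, normal approximation:

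| n per arm | SE, correct | SE, as written | Power, correct | Power, as written |
|---|---|---|---|---|
| 13 | √(1.2/13) = 0.304 | √(4/13) = 0.555 | P(Z > 1.96 − 1.481) = 32% | P(Z > (1.087 − 0.45)/0.304) = 2% |
| 10 | √(1.2/10) = 0.346 | √(4/10) = 0.632 | P(Z > 1.96 − 1.299) = 25% | P(Z > (1.240 − 0.45)/0.346) = 1% |

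Small-sample critical values lower the correct-model power by a few points; simulation at 13 per arm gave about 29% against 2%. Mixed-model fits at 10 per arm and ρ = 0.7 (300 replicates) gave an empirical SD of the estimate of 0.345. The mean model SE was 0.341 with subject as the upper level and 0.623 as written.

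**(b) Mean of T2 and T3 minus mean of T0 and T1, 13 per arm, ρ = 0.7**

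- Correct SE: √(2 × 0.3/13) = 0.215. As written: √(2/13) = 0.392. The ratio is again 1.83.
- Simulated power for 0.45 SD: about 51% against 8%.

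**(c) Group difference averaged over all four visits**

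- The true variance is 1 + 3ρ times what the model assumes: 3.1 at ρ = 0.7.
- False rejection: 2·P(Z > 1.96/√3.1) = 2·P(Z > 1.113) = 27%.
- At ρ = 0.5: 2·P(Z > 1.96/√2.5) = 22%. At ρ = 0.8: 2·P(Z > 1.96/√3.4) = 29%.

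**The case against.** The strongest reply is that this is a slip of the pen. The paragraph directly above has the right order, and the Discussion stresses within-subject analysis, so the authors plainly know that visits nest in people. A competent analyst would probably correct it without comment, and none of the figures above would then arise.

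Four further points limit the consequences.

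- The 27% false-rejection figure belongs to a visit-averaged contrast. Two of those visits precede allocation, and the protocol sets change as the target. For change, the error is conservative.
- The outcomes section lists pairwise changes, so the T1-to-T2 loss (about 32% to 2%) is the fairer illustration than the pooled pre/post contrast.
- The 0.45 is an effect of CR, not of tDCS.
- This is a pilot. Its tDCS aim is only an indication of added effect, and the Discussion already concedes low power. With complete data the estimated difference in change is the same under either order.

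All of these stand, but they concern emphasis. None makes the sentence right. Equality of the point estimates needs complete data, whereas the plan expects 20% drop-out. Even a search for a trend needs an honest interval, and one about 1.8 times too wide would hide it. A silent correction would leave the published model and the fitted model different for the one randomised comparison.

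**Conclusion.** The concern holds: the model statement for active versus sham tDCS is wrong as written and contradicts the paragraph before it. The document fixes the structure and fixes it incorrectly, so this is not detail left to an analysis plan.

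For the stated target the error makes the test far too conservative: the SE is inflated 1.41 to 3.16 times for ρ from 0.5 to 0.9, and most of the power is lost. The opposite error, roughly 22% to 29% false rejection for ρ from 0.5 to 0.8, applies only if the looser phrase about mean differences between the groups is read as a visit-averaged comparison. In neither case could the p-value or interval be relied on.

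The sizes rest on the assumed correlation, equal correlation across visits, and a literal fit. The contradiction and the direction of error for each contrast hold for any positive within-person correlation. The sample size and the feasibility and acceptability outcomes are unaffected.

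**What to change.** Correct the sentence in the paragraph on CR + active tDCS vs. CR + sham tDCS to match the paragraph above it: time point of assessment at level 1, nested within subject at level 2, with a random subject intercept. State that the active-versus-sham effect is the arm-by-time contrast for the changes already listed under the primary outcome measures, so that the model answers the question set under Superior effect of active tDCS.

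Make the correction before the allocation envelopes are opened and record it as a protocol clarification. It takes one sentence, with no new data, no change to the sample size and no burden on participants.

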#### Interim analyses {21b}

Not applicable; no interim analyses will be performed.

#### Methods for additional analyses (e.g., subgroup analyses) {20b}

Not applicable; there are no additional analyses planned because of the small sample size.

#### Methods in analysis to handle protocol non-adherence and any statistical methods to handle missing data {20c}

Data will be analyzed according to intention-to-treat principles. The extent of missing data will be explored in the outcomes and predictors of missingness will be examined.

#### Plans to give access to the full protocol, participant-level data, and statistical code {31c}

This document is the full protocol. Participant-level data and statistical code will be available from the corresponding author on reasonable request.

### Oversight and monitoring

#### Composition of the coordinating center and trial steering committee {5d}

The trial is coordinated and steered by the investigators of this study. The project management group (AP, LB, and LM) provides the day-to-day support for this trial. AP is responsible for the identification of potential participants, recruitment, taking consent, coordinating data collection, overseeing adherence to the study protocol, and keeping the participants involved during the waiting period (see “Discussion”). LB and LM supervise AP in all of these steps and will monitor the progress and the conduct of the study. DD and GM provide supervision for the cognitive remediation training. The progress and conduct of the study and any identified or planned deviations from the study protocol will be discussed with BC and GM. All authors will contribute to writing the manuscript describing the results of the trial.

